**Expected start date : February 2005**

**Expected trial duration : 30-36 months**

**SYNOPSIS**

| **Title** | **Low dose adrenaline, promethazine, & hydrocortisone (alone and in combination) to prevent acute adverse reactions to antivenom in people bitten by snakes: randomised, double-blind, placebo-controlled trial** |
| --- | --- |
| Aim | Investigation of the efficacy and safety of pretreatment with adrenaline, promethazine & hydrocortisone (alone and in combination) in comparison with placebo to prevent acute adverse reactions to antivenom |
| Design | Type: a randomised, double-blind, placebo-controlled study  Number of centres: three  Estimated duration: six months – one year  Design: factorial 2x2x2 design |
| Sample size | At least 1000 patients are required to have 80% power at p<0.01 to detect a 25% reduction in the rate of acute adverse reactions to antivenom |
| Indication | Snakebite with evidence of systemic / severe local envenomation |
| Patient selection I | Inclusion criteria   - Age above 12 yrs - Patients admitted to hospital after snakebite in whom antivenom is indicated - Patients who give informed consent |
| Patient selection II | Exclusion criteria   - Patients in whom adrenaline may be contraindicated - Patients currently taking beta- or alpha-adrenoceptor antagonists, and tricyclic antidepressants - Pregnant and nursing women |
| Trial medication | Drugs: adrenaline, promethazine, & hydrocortisone alone and in combination  Placebo: 0.9% NaCl  Duration of treatment: once as pretreatment before antivenom |
| Efficacy variables | Efficacy:   - Reduction in acute adverse reactions to antivenom   Safety:   - Adverse reactions to trial medications |

**BACKGROUND TO THE STUDY**

The overall incidence of snakebite in Sri Lanka exceeds 400 per 100,000 population per year, one of the highest in the world. In the North-Central and North-Western provinces of the country, where snakebite incidence is particularly high, three regional hospitals reported 1851 admissions with 11 deaths due to snakebite during 2000 [Ministry of Health, Sri Lanka, 2002]. Although there are more than 90 species of snakes in the country, much of the morbidity and about 95% of the mortality associated with snakebites are due to the highly venomous cobra, Russell’s viper, and kraits [De Silva & Ranasinghe, 1983].

Polyvalent antivenom is the most effective, if not the only effective treatment available for snakebite envenomation in Sri Lanka. Acute adverse reactions to the antivenom are common [Karunaratne & Anandadas, 1973] and include anaphylaxis. Reaction rates ranging from 43% [Premawardena et al., 1999] to 81% [Ariaratnam et al., 2001] have been reported. In most cases symptoms are mild: urticaria, nausea, vomiting, diarrhoea, headache, and fever; but in up to 40% of cases severe systemic anaphylaxis develops, with bronchospasm, hypotension, or angio-oedema [Malasit et al., 1986]. Even though Fab antivenoms are thought to be less immunogenic, a recent comparative study reported an acute reaction rate of 48% [Ariaratnam et al., 2001]. As a result, the management of acute adverse reactions to antivenom is an important part of the management of snake envenoming in Sri Lanka. Increasing the safety of treatment with antivenom for snakebite victims is therefore a matter of high priority.

Several methods have been used to reduce acute adverse reactions to antivenom. A small test dose of antivenom to detect patients who may develop acute adverse reactions to the antivenom has no predictive value, can itself give rise to anaphylaxis, and is no longer recommended [Malasit et al., 1986]. Prophylactic use of hydrocortisone and antihistamines before infusion with antivenom is also practised widely, although the theoretical basis for their use is unclear. Antihistamines counter only the effects of histamine after its release and do not prevent further release, and one small randomised controlled trial demonstrated no benefit from the routine use of antihistamines [Fan et al., 1999]. Hydrocortisone takes time to act and may be ineffective as a prophylactic against acute adverse reactions that can develop almost immediately after antivenom treatment, which is very often administered urgently to snakebite victims. A recent study suggests that intravenous hydrocortisone is ineffective in preventing acute adverse reactions to antivenom, but if given together with intravenous chlorpheniramine (an antihistamine) it may reduce these reactions [Gawarammana et al., 2004]. However, this trial recruited only 52 patients and was not designed to study the efficacy of chlorpheniramine alone, making clear interpretation of the results and recommendations on pretreatment with steroids and antihistamines to prevent acute reactions to antivenom difficult.

In one study of 105 patients low-dose adrenaline given subcutaneously immediately before administration of antivenom to snakebite victims significantly reduced the incidence of acute adverse reactions to the serum [Premawardena et al., 1999]. However, the authors were unable to enrol sufficient participants to adequately establish safety, a major concern regarding the use of adrenaline in a prophylactic role [Khanna & Hawkins, 1999], particularly the risk of intra-cerebral haemorrhage [Dassanayake et al., 2002; Horowitz et al. 1996]. Therefore, further studies on the safety of this treatment are required before it can be recommended routinely.

For the present, the only available alternative to prevention is the early detection of adverse reactions to antivenom and the ready availability of drugs such as adrenaline for their prompt treatment. Therefore, the need for a properly controlled trial to study the safety and efficacy of all possible pretreatment medications to prevent acute adverse reactions to antivenom is clear.

# TRIAL DESIGN

**Objective**

To determine whether low-dose adrenaline, promethazine, and hydrocortisone, alone and in different combinations, are significantly better than placebo in the prevention of acute adverse reactions to antivenom in snakebite victims. The principle outcomes will be the development of acute reactions to antivenom. This study also aims to assess the safety of pretreatment medication used before the administration of antivenom.

**Design**

This is a multicentre, double-blind, randomised, placebo-controlled, factorial design clinical trial, to be conducted in two State hospitals in Sri Lanka. The participating hospitals are: General Hospital, Kurunegala and General Hospital, Polonnaruwa, and Base Hospital, Embilipitiya.

**Sample size and predicted events**

We estimate that acute adverse reactions occur in about 40% of patients who receive antivenom. Therefore, proportional reductions of 25-40% of acute adverse reactions would correspond to substantial absolute benefits (see Table). For an anticipated 25% reduction in adverse reactions from the current reaction rate by any one treatment with 80% power at p<0.01 using the proposed design, a sample size of 1000 would be needed for this study.

During the trial it is intended that blinded event rates (i.e. active and placebo groups combined) will be monitored and, if they are substantially lower than anticipated, the TSC will have the option of increasing the sample size.

**Table: Statistical power to detect 25-40% proportional reductions in acute adverse reactions to antivenom among 1000 randomised patients (based on 40% control group event rate)**

| **Proportional**  **reduction** | **Control group**  **500** | **Treatment group**  **500** | **Power for a type I error <0.01** | **Power for a type I error <0.05** | **Events avoided per 1000 treated** |
| --- | --- | --- | --- | --- | --- |
| 40% | 200 | 120 | >95% | >99% | 80 |
| 30% | 200 | 140 | 95% | >95% | 60 |
| 25% | 200 | 150 | 80% | >90% | 50 |

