# ASSESSMENT OF OUTCOME

**Primary outcomes:**

The primary analysis will compare the frequency of **severe reactions** to antivenom in the first 48 hours, among all those allocated each separate treatment versus all those allocated placebo for that treatment, i.e.:

1. all those allocated adrenaline versus all those allocated no adrenaline
2. all those allocated promethazine versus all those allocated no promethazine
3. all those allocated hydrocortisone versus all those allocated no hydrocortisone

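### The sample size and its 80% power are calculated for any acute reaction at a 40% rate, but the primary outcome is severe reactions, for which the protocol gives no control rate and no power

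*Protocol*

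**What the plan says.** **Basis of the sample size.** The protocol's section Sample size and predicted events begins: "We estimate that acute adverse reactions occur in about 40% of patients who receive antivenom". For a 25% reduction it concludes: "with 80% power at p<0.01 using the proposed design, a sample size of 1000 would be needed for this study". The power table has the same basis, as its title shows: "reductions in acute adverse reactions to antivenom among 1000 randomised patients (based on 40% control group event rate". The Synopsis describes the 1000 patients as enough "to detect a 25% reduction in the rate of acute adverse reactions to antivenom".

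**Primary outcome.** Under Primary outcomes: "The primary analysis will compare the frequency of severe reactions to antivenom in the first 48 hours". Secondary outcomes then lists reactions of any grade within 48 hours. The Data Monitoring section also frames the interim decision as a net difference in severe reactions.

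**Objective.** Here no severity limit appears: "The principle outcomes will be the development of acute reactions to antivenom".

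**Severe rate.** No planning figure is given. The nearest is in the Background, after cited reaction rates of 43% to 81%: "in up to 40% of cases severe systemic anaphylaxis develops, with bronchospasm, hypotension, or angio-oedema".

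**The concern.** Power for a binary outcome depends heavily on its control rate. Severe reactions are a subset of all reactions, so their rate cannot exceed the 40% used for planning and is probably well below it; the Background itself says that symptoms are mild in most cases. All three primary comparisons (adrenaline, promethazine, hydrocortisone) use the severe outcome. If their true power is far below the printed 80%, a null result could be read as evidence that a treatment does not work when the trial had little chance of showing the effect it was planned for.

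**Working it through.** **Inputs.** 500 versus 500 patients, which are the margins of the factorial (power table). Two-sided tests (Methods of analysis). Reductions of 25%, 30% and 40%, and alpha of 0.01 and 0.05 (power table).

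**Formula.** Two proportions with pooled variance, p2 = p1 × (1 − reduction), pbar = (p1 + p2)/2:

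power = Φ{ [p1 − p2 − z × √(2·pbar·(1 − pbar)/500)] / √([p1(1 − p1) + p2(1 − p2)]/500) }, with z = 2.576 at 0.01 and 1.960 at 0.05.

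**1. The plan's own figure.** The row is "25% | 200 | 150 | 80% | >90% | 50". With p1 = 0.40, p2 = 0.30 and pbar = 0.35, the two standard errors are 0.03017 and 0.03000. Power at 0.01 = Φ[(0.10 − 2.576 × 0.03017)/0.03000] = Φ(0.743) = 77.1%. At 0.05 it is 91.4%, which agrees with the table. The 80% is reproduced only approximately, and 80% power would need 1060 patients. That gap is small. It does confirm that the table rests on the 40% any-reaction rate.

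**2. Control rate needed for 80% power.** For a 25% reduction at 0.01, raising p1 until the formula gives 80% yields p1 of about 0.416, or 42%.

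**3. Illustrative severe rates.** Assume that 40% of reactions are severe, the Background's upper figure:

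- planning rate: 0.40 × 0.40 = 16%
- lowest cited reaction rate: 0.43 × 0.40 = 17.2%
- highest cited reaction rate: 0.81 × 0.40 = 32.4%

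Worked example at 16%: p2 = 0.12, pbar = 0.14, standard errors 0.02195 and 0.02191. Power at 0.01 = Φ[(0.04 − 2.576 × 0.02195)/0.02191] = Φ(−0.754) = 22.5%.

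| Control rate | Source | 25%, α 0.01 | 25%, α 0.05 | 30%, α 0.01 | 40%, α 0.01 |
| --- | --- | --- | --- | --- | --- |
| 40% | plan, any reaction | 77.1% | 91.4% | 92.5% | 99.8% |
| 32.4% | 81% × 40% | 60.5% | 81.2% | 80.8% | 98.3% |
| 17.2% | 43% × 40% | 25.0% | 47.7% | 39.5% | 72.1% |
| 16% | 40% × 40% | 22.5% | 44.5% | 35.8% | 67.6% |
| 10% | assumed, no source | 11.9% | 28.7% | 19.0% | 40.3% |

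**4. What 1000 patients could detect.** At a 16% control rate, 80% power at 0.01 needs a reduction of about 45%. A 25% reduction would need about 3,500 patients.

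**5. The blinded review.** The steering committee may enlarge the trial if blinded event rates fall well below what was anticipated. The only anticipated rate is 40% for any reaction. That rate could be on target while severe reactions are far too few.

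**The case against.** - **The severe rate is unknown, so no single power figure is a fact.** This stands. The 16% multiplies two figures from different sections, and the 10% has no source in the protocol. A reader might infer that power for the primary outcome is simply in the single digits or low twenties; the document does not support that. The cited reaction rates carry the illustration up to 60%, and larger reductions or alpha 0.05 do better still (at 16% and alpha 0.05, a 40% reduction has 86% power). Applying the planned 25% reduction to severe reactions is also an assumption.

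- **16% is not a ceiling.** This also stands. The Background counts bronchospasm and angio-oedema as severe. The grading under Secondary outcomes puts bronchospasm among moderate reactions, but counts cyanosis, confusion and altered consciousness as severe. The two definitions overlap and neither contains the other.

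- **There is only one formal primary outcome.** Largely right. A reader might infer that the protocol names two rival primary outcomes and leaves the choice open until the data are seen. However, the Primary outcomes, Secondary outcomes and Data Monitoring sections agree with one another, and a severe reaction is an acute reaction. The Synopsis and Objective are loosely worded and should be aligned. The substantive conflict is between the sample size and the primary outcome.

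- **The sample size can be increased.** True, but the step is optional and is not tied to severe reactions.

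**Conclusion.** The point holds. The only power calculation in the protocol describes a secondary outcome, and the stated 80% does not apply to the primary comparisons. This part needs no assumed severe rate: 80% power at 0.01 for a 25% reduction requires a control rate of about 42%, while severe reactions are a subset of the planned 40%. The highest severe rate that can be built from the protocol's figures, 32.4%, also falls short.

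The size of the shortfall is conditional. If severe reactions make up 40% of all reactions, power for a 25% reduction at 0.01 is about 22% at the planning rate and 25% to 60% across the cited reaction rates. A lower severe rate gives less, for example 12% at an assumed 10%. These are illustrations and not estimates of the trial's actual power.

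**What to change.** Name one primary outcome in the same terms in the Synopsis, Objective, Sample size and Primary outcomes sections.

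- **If severe reactions stay primary:** state an assumed control rate for severe reactions under the protocol's own grading, with a range. Recompute the power table and the detectable reduction on it. Label the present table as applying to the secondary outcome of any reaction. Tie the blinded event-rate review to the pooled severe rate, with the anticipated value stated.
- **If any acute reaction is intended:** make it primary under Primary outcomes, with severe reactions as the key secondary outcome, and align the interim criterion.

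Either route costs some wording; the first also needs a recalculated table. The first route makes the stated power less favourable. Correcting the document needs no extra patients, but restoring 80% power for a 25% reduction in severe reactions would: about 3,500 in total at a 16% rate. Otherwise the protocol should say openly that only larger reductions are detectable.

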**DATA ANALYSIS**

# Methods of analysis

The fundamental assessments of efficacy will involve comparisons of the proportions of patients experiencing an event among all the randomised patients in their originally allocated treatment group, irrespective of what treatment they were actually given (i.e. “intention-to-treat” analyses). Two-sided P values will be used. No allowance will be made for multiple hypothesis testing in the primary comparison of each of the three study treatments in this 2 x 2 x 2 factorial study. For secondary and, particularly, for tertiary comparisons, allowance will be made for multiple hypothesis testing, taking into account the nature of the events (including timing, duration, and severity) and evidence from other studies.

The independent effects and effects of interactions of the three interventions will be assessed by using Cox regression. Cox regression will be used with a constant time to event for all subjects as we are only interested in reaction rate and not in the time to reaction.

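### The stated powers of 80% and 95% at p<0.01 are about 3 points too high on the table's own inputs, and the 40% control rate rests on an unstated assumption about the other two trial drugs

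*Protocol*

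**What the plan says.** The sample size section of the protocol starts from "We estimate that acute adverse reactions occur in about 40% of patients who receive antivenom". It then asks for 1000 patients: "For an anticipated 25% reduction in adverse reactions from the current reaction rate by any one treatment with 80% power at p<0.01". The synopsis repeats the claim as a minimum: "At least 1000 patients are required to have 80% power at p<0.01".

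The power table, "based on 40% control group event rate", sets 500 control against 500 treated patients. Its columns are the proportional reduction, control events, treated events, power at 0.01, power at 0.05, and events avoided. The two rows at issue are:

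- "25% | 200 | 150 | 80% | >90% | 50"
- "30% | 200 | 140 | 95% | >95% | 60"

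Under Methods of analysis the protocol fixes the sidedness, "Two-sided P values will be used", and the handling of the three primary comparisons: "No allowance will be made for multiple hypothesis testing in the primary comparison of each of the three study treatments". The Treatment plan and Assessment of outcome sections define each primary comparison as a factorial margin, that is, everyone allocated a drug against everyone not allocated it, whatever else they receive. The sample size section also lets the steering committee enlarge the trial if blinded event rates, all groups combined, turn out well below expectation. It does not say what combined rate is expected.

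**The concern.** There are two separate matters.

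First, the table gives every input needed to check its power figures, and two of the three entries at 0.01 do not follow from them. One of these is the headline claim that justifies 1000 patients.

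Second, the control group for each drug is not an untreated group. In a 2 x 2 x 2 design with equal cells, the 500 patients without adrenaline, for example, fall into four cells: no active drug, promethazine alone, hydrocortisone alone, and both. Three quarters of them therefore receive at least one other trial drug. If those drugs work, the margin's event rate lies below the no-drug rate, and a fixed proportional reduction becomes a smaller absolute difference. The table uses 40% for the whole margin without comment.

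What is at stake is the reader's picture of the power, and how the blinded event-rate check is read: a combined rate below 40% could mean a low baseline or effective drugs.

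**Working it through.** **Inputs.** From the power table: n = 500 per margin; 200 v 150 events (40% v 30%) and 200 v 140 events (40% v 28%); type I error 0.01. From Methods of analysis: two-sided, no multiplicity adjustment, so z = 2.576.

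**Formula.** Power = Φ[(p1 − p2 − z·s0)/s1], where p̄ = (p1 + p2)/2, s0 = √(2p̄(1 − p̄)/n) and s1 = √((p1(1 − p1) + p2(1 − p2))/n).

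**25% row (stated 80%).** p̄ = 0.35, s0 = 0.03017, s1 = 0.03000. (0.10 − 2.576 × 0.03017)/0.03000 = 0.743, and Φ(0.743) = 77.1%.

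**30% row (stated 95%).** p̄ = 0.34, s0 = 0.02996, s1 = 0.02972. (0.12 − 2.576 × 0.02996)/0.02972 = 1.441, and Φ(1.441) = 92.5%.

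**Size for the stated power.** n per margin = [(z√(2p̄(1 − p̄)) + z_β√(p1(1 − p1) + p2(1 − p2)))/(p1 − p2)]². For 40% v 30% at 80% power this is 530, or 1060 in total. For 40% v 28% at 95% power it is 552, or 1104 in total.

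**Does another formula give the stated figures?**

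| Method at 0.01 | 40% v 30% | 40% v 28% |
|---|---|---|
| Stated | 80% | 95% |
| Two-sided, as above | 77.1% | 92.5% |
| Two-sided, unpooled variance | 77.6% | 92.8% |
| Two-sided, exact Pearson | 77.2% | 92.6% |
| Two-sided, continuity-corrected | 75.1% | 91.5% |
| One-sided | 84.0% | 95.5% |
| One-sided, continuity-corrected | 82.3% | 94.8% |

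A one-sided test comes close to the 95%, but not to the 80% or the 1000 (it needs 912, or 952 with continuity correction), and it contradicts the two-sided rule. None of the methods tried gives all three stated figures together.

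**The other cells hold.** 40% v 24% gives 99.8% at 0.01 and over 99.9% at 0.05. At 0.05, 40% v 28% gives 98.0% and 40% v 30% gives 91.4%.

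**Control margin.** Assume a no-drug rate of 40%, multiplicative effects, equal cells, and the protocol's own 25% reduction for each effective drug. Half of any control margin receives a given other drug, so each effective other drug multiplies the margin rate by (1 + 0.75)/2 = 0.875.

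| Other drugs that work | Control rate | Treated rate | Power at 0.01 | Power at 0.05 | N for 80% at 0.01 |
|---|---|---|---|---|---|
| None | 40% | 30% | 77.1% | 91.4% | 1060 |
| One | 0.40 × 0.875 = 35.0% | 26.25% | 66.6% | 85.2% | 1294 |
| Both | 0.40 × 0.875² = 30.6% | 23.0% | 56.3% | 78.1% | 1562 |

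Read the other way, a margin rate of 40% with both other drugs effective implies a no-drug rate of 0.40/0.875² = 52%.

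**Pooled blinded rate, on the same assumptions.** No drug works: 40%. One works: 0.40 × 0.875 = 35%. All three work: 0.40 × 0.875³ = 26.8%.

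**The case against.** The arithmetic shortfall is small against the precision of the inputs. The 40% is itself approximate, and four of the six power cells are only lower bounds. A control rate of 41.5% would give 80% in the 25% row, and 42.6% would give 95% in the 30% row. Both lie below 43%, the lowest rate quoted in the Background. This argues that the error is modest. It does not make the table right, because the table names 40% and gives the event counts.

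A reader might go further and infer that the 40% control rate is wrong for a factorial margin. The protocol does not support that. The rate falls below 40% only if 40% is the rate with no active drug and at least one other drug works, and neither is established. The protocol calls its figure the current rate among patients given antivenom, and the Background says that hydrocortisone and antihistamines are already in wide prophylactic use. The Background also doubts that either of these works. A no-drug rate of 52% would fit the 43% to 81% reported there. What stands is that the assumption is needed and is not stated.

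Nor is the blinded check simply a further defect. The protocol does not say that its reference rate is 40%, and the table's 25% row already implies (200 + 150)/1000 = 35%. A low combined rate reduces power whatever its cause, so the option to enlarge the trial is a partial safeguard. It would be easier to use with the expected rates written down.

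**Conclusion.** The point holds in two parts.

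The first is an error in the text. Under the two-sided test, the 80% should be about 77%, the 95% should be about 92.5%, and 80% power needs about 1060 patients, not 1000. The overstatement is about 3 points of power, or 60 patients (6%). It rests on nothing beyond the table and the sidedness rule.

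The second is an unstated assumption. Using 40% for the control margin requires either that the other drugs leave the rate unchanged or that the no-drug rate is higher. If 40% is the no-drug rate and effects multiply, power at 0.01 is about 67% with one other drug effective and about 56% with both. The last figure is the unfavourable end of the scenarios and should not be read as the trial's expected power. At 0.05, which the table also shows, the two figures are about 85% and 78%.

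All of these figures concern any acute reaction. The primary outcome in Assessment of outcome is severe reactions, so neither the stated powers nor the corrected ones describe the primary comparison.

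**What to change.** 1. In the 0.01 column, restate the 25% row as about 77% and the 30% row as about 92.5%. Restate the synopsis and the sample size paragraph as about 77% power with 1000 patients.
2. Label these figures as power for any acute reaction, not for the severe-reaction primary outcome.
3. State that 40% is assumed for the whole control margin and what that implies about the other drugs. Add the scenarios with control rates of 35% and 30.6%, giving power for a 25% reduction at both levels: about 67% and 56% at 0.01, and about 85% and 78% at 0.05.
4. For the blinded check, state the expected combined rate: 40% if no drug works, 35% if one does, and about 27% if all three do.

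The cost is protocol wording and a slightly less favourable power statement. Enrolment does not change.
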